**METHODOLOGY**

**Description of the type of trial**

A prospective, single-blind, randomized controlled trial will be carried out in two PC health centers in Cantabria (Camargo Costa and Camargo Interior). Patients attending their PC center with possible common mental disorders (related to anxiety, depression or somatization) not susceptible to be referred to specialized care according to the criteria of their referring physician in the health center, will be invited to participate in the study, as well as to sign the informed consent form. Those who accept will be assessed before being assigned to groups, so the assessors will be blinded to treatment assignment at all times. Cases who have completed testing will be randomly assigned to the two treatment conditions: (i) control group with treatment using Bernstein and Borkovec's progressive muscle relaxation techniques together with treatment as usual by their GP; or (ii) experimental group with manualized group treatment based on CBT plus treatment as usual by their GP.

Patients assigned to both groups will receive 7 sessions of 1.5 hours duration, in subgroups of approximately 10-12 persons, spread over 12 weeks, with a higher temporal frequency at the beginning of the treatment (one session per week) and progressive extension of the time interval between sessions as the treatment progresses.

**Sample size:**

The study will recruit 300 participants (150 for each arm).

**Name of each arm:**

| Arms | Assigned Interventions |
| --- | --- |
| Experimental: transdiagnostic cognitive-behavioural therapy (TD-CBT)  Transdiagnostic group cognitive-behavioural therapy: The psychological interventions will be manualized. Patients assigned to the experimental group will receive 7 sessions (1.5 hr/session) in groups of approximately 8-10 individuals over a 12-week period. | Behavioural: Transdiagnostic cognitive-behavioural therapy (TD-CBT). |
| Active Comparator: Relaxation therapy  The control group will receive a PMR group intervention, based on the Bernstein and Borkoveck procedure. Patients will receive 7 sessions (1.5 hr/session) in groups of 8-10 individuals over a 12-week period. | Bernstein and Borkovec progressive muscle relaxation (PMR) |

**Recruitment process of participants**

In a first step, GP, as they usually do among those patients who would not be referred to specialised care, will recruit potential candidates with a common mental disorder (anxiety disorders, mild or moderate depression, somatoform disorders) as the main reason for consultation (Phase 1), then psychologists trained with the appropriate tools for the detection of mental disorders will make a correct diagnosis of those disorders of mild and moderate intensity to be treated in PC according to the previously established inclusion and exclusion criteria (Phase 2). If the criteria are met, random allocation to groups will be carried out by blinded research staff, not involved in the assessment or treatment. In the case of not meeting the criteria, the subject would be discarded, recommending consultation with their GP or, if necessary, referral to the Mental Health Centre of reference for their area.

In the post-treatment phase, a psychologist who had not participated in the psychological treatment group would carry out the evaluation phase with the same tests used in the pre-treatment evaluation. This researcher would be blind to the branch of the study to which the assessed subject belongs. The patient will be asked not to disclose which group he/she participated in at any time during the study.

**Ethical considerations**

The proposed research respects and will comply with current legislation and other regulatory standards relevant to the project in the field of ethics, including the fundamental principles of the Declaration of Helsinki, the Council of Europe Convention on Human Rights and Biomedicine, the UNESCO Universal Declaration on the Human Genome and Human Rights, and the Convention for the Protection of Human Rights and Dignity of the Human Being with regard to the Application of Biology and Medicine.

This study will be developed according to the following criteria:

- Briefly explain the ethical principles justifying the research in accordance with international and national regulations.

- Clearly state the risks and safety assurances provided to participants.

- Establish that the research will be carried out when authorisation is obtained from: the legal representative of the research institution and the institution where the research will be carried out; the Informed Consent of the participants; and the approval of the project by the Research Ethics Committee of the institution.

**Inclusion/Exclusion criteria**:

Inclusion criteria:

- Patients aged 18 to 65, inclusive, who present to the primary care centre seeking treatment for anxiety, depressive or somatic symptoms.

- Scores above the predetermined cut-off points on the GAD-7 (>= 10), the PHQ-9 (>= 10) or the PHQ-15 (>=10 plus a score of 2 in three or more somatic symptoms).

- Agreement to participate in the study, with written informed consent.

Exclusion criteria:

- Major depressive disorder (PHQ-9> 24) and/or severe disability (SDS > 25) will be interviewed by a clinician for the presence of any severe mental disorder, including autism spectrum disorders, bipolar disorder, schizophrenia, anorexia nervosa, substance dependence, personality disorder.

- Presence of severe or recent suicide attempts

- Presence of intellectual disability (IQ < 70).

- Be receiving psychological treatment or any type of specialized care related to mental health.

- Insufficient Spanish language skills

**Outcome Measures**

Primary Outcome Measures:

- Change in cost-effectiveness data [Time Frame: Baseline, immediately after the intervention, and 12-month follow-up]

Cost-effectiveness results will be calculated by the ICER, defined as the difference in mean costs between interventions divided by the difference in their effectiveness according to the symptom questionnaires’ mean scores.

The healthcare data collected will be used for cost calculations. To calculate healthcare-related costs, an ad hoc questionnaire will be used to collect emotional disorder-related healthcare data (public and private healthcare consultations, accidents, medical tests, and sick leaves in the past 3 months; psychotropic drugs or other medication, and their posology).

- Change in cost-utility data [Time Frame: Baseline, immediately after the intervention, and 12-month follow-up]

Cost-utility will be measured through the healthcare data collected above and the European Quality of Life Scale (EuroQoL, EQ) [71], calculating the QALYS and the ICURs, defined as the difference in mean cost divided by the difference in mean QALYs. The Spanish version of the 5-domain, 5-level EuroQol (EQ-5D-5L) [72,73] will be used to assess health status in five dimensions (mobility, self-care, daily activities, pain/unease, and anxiety/depression) with five levels of severity (no problems, slight problems, moderate problems, severe problems, and either extreme problems or unable to perform activity). The scores obtained in the different dimensions can be combined to create a 5-digit code describing the patient's state of health, being able to stablish up to 3125 different combinations, and therefore, different possible health states. This system was converted into a utility score using the value set for Spain from the EQ-5D-5L Crosswalk Index Value downloaded from the EuroQol website (<https://euroqol.org/euroqol/>).

Secondary Outcome Measures:

- Change in depressive symptoms: Patient Health Questionnaire - 9 item (PHQ-9) [Time Frame: Baseline, immediately after the intervention, and 12-month follow-up]

The PHQ-9 [54] is the depression module of the PHQ [74, 75] that scores the 9 DSM-IV depression criteria in the last two weeks. Is a nine item, self-report scale that ranges from 0 to 27 (higher scores means a worse outcome).

- Change in anxiety symptoms: Generalized Anxiety Disorder - 7 item (GAD-7) [Time Frame: Baseline, immediately after the intervention, and 12-month follow-up]

The GAD-7 [56] assesses common anxiety symptoms in the last two weeks. It is composed of seven self-report items ranging from 0 to 21 points. Higher scores means a greater presence of anxiety symptoms.

- Change in somatic symptoms: Patient Health Questionnaire - 15 item (PHQ-15) [Time Frame: Baseline, immediately after the intervention, and 12-month follow-up]

The PHQ-15 [58] is the somatization module of the PHQ and scores symptoms present in the past four weeks. The scale is composed of fifteen self-report items, ranging from 0 to 30. Higher scores means a worse outcome.

- Change in functioning: Sheehan Disability Scale (SDS) [Time Frame: Baseline, immediately after the intervention, and 12-month follow-up]

The SDS [59] is a five item self-reported scale composed of three main domains (work, family and social functioning) and two optional items (perceived stress and perceived social support). It ranges from 0 to 50, with higher scores indicating a worse outcome.

- Change in treatment satisfaction [Time Frame: Immediately after the intervention and 12-month follow-up]

Posttreatment and 12-month follow-up assessments will also collect an additional question about treatment satisfaction, through a Likert-type question, ranging from 0 to 10.

Other mechanistic outcome measures:

- Change in rumination: Ruminative Responses Scales (brooding subscale) (RRS-B) [Time Frame: Baseline, immediately after the intervention, and 12-month follow-up]

The RRS-B [76] is composed of five self-reported items, ranging from 5 to 20. Higher scores means a worse outcome.

- Change in worry: Penn State Worry Questionnaire – Abbreviated (PSWQ-A) [Time Frame: Baseline, immediately after the intervention, and 12-month follow-up]

The PSWQ-A [62] measures the pathological worry as an uncontrollable and general state. The scale is composed of eight self-reported items, ranging from 5 to 40. Higher scores means a worse outcome.

- Change in attentional and interpretative biases: Inventory of Cognitive Activity in Anxiety Disorders (IACTA) [Time Frame: Baseline, immediately after the intervention, and 12-month follow-up]

The IACTA was originally developed by [name] [63]. It includes subscales that assess distortions according to Eysenck's four-factor theory [77]. The scale is composed of five self-reported items, ranging from 0 to 20. Higher scores means a worse outcome.

- Change in emotion regulation: Cognitive Emotion Regulation Questionnaire (CERQ) [Time Frame: Baseline, immediately after the intervention, and 12-month follow-up]

The CERQ-36 [78] was developed for measuring the specific cognitive emotion regulation strategies that a person uses to face a stressful event (self-blame, acceptance, rumination, positive refocus, refocus on planning, positive reappraisal, putting into perspective, catastrophizing or blaming others). It scores from 1 ("almost never") to 5 ("almost always") how often the participant thinks as described. The 27-item shortened version will be used [79]. Each cognitive strategy is assessed by means of three items, ranging from 3 to 15. Higher scores means a greater use of the strategy.

- Change in metacognitive beliefs: Metacognitions Questionnaire (negative beliefs subscale) (MCQ) [Time Frame: Baseline, immediately after the intervention, and 12-month follow-up]

The MCQ-NB [65] is a short form of the original MCQ [80], which measures the beliefs about the own thinking processes. The scale is composed of six self-reported items, ranging from 6 to 24. Higher scores means a worse outcome.

- Change in Cognitive Distortions in Emotional Disorders (CDTE) [Time Frame: Baseline, immediately after the intervention, and 12-month follow-up]

The CDTE [81] measures the frequency of certain cognitive biases. It includes sixteen self-reported items that measure the presence of four factors: sustained attention bias, divided attention bias, magnification interpretational bias, and catastrophization interpretational bias. It ranges from 0 to 4. Higher scores means a greater presence of the cognitive bias.

- Change in alliance: Working Alliance Inventory Patient Form (WAI-P) and Group Session Rating Scale (GSRS) [Time Frame: In therapy sessions number 1, 4 and 7]

The WAI-P [69] is a thirty-six self-report scale that measure perceived therapeutic alliance. It ranges from 36 to 252 with higher scores indicating better alliance between patient and clinical professional.

The GSRS [70] is a four item self-reported scale that assess alliance to the group. It ranges from 0 to 40, with higher scores indicating better alliance between the patient and the group of therapy.

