**Abstract:**

The aim of this study is to test the cost-effectiveness and cost-utility of adding a transdiagnostic group cognitive-behavioural therapy (TD-CBT) to treatment as usual (TAU) for emotional disorders in primary care . A single-blind randomized controlled clinical trial will be conducted to compare the TD-CBT group therapy plus TAU to progressive muscle relaxation (PMR) group plus TAU in individuals, aged 18 to 65, with emotional disorders in four primary care centres located in Cantabria, Spain. The study will take a societal perspective. Psychological assessments will be carried out at baseline, post-treatment, and 12-months follow-up. The assessments will include measures of clinical symptoms (anxiety, depression, and/or somatic), dysfunction, cognitive-emotional factors (ruminative processes, pathological concern, attentional and interpretative biases, emotion regulation strategies and meta-cognitive beliefs), and satisfaction with the treatment received. Data on health service use, including medication and days of absence from work, will be collected from electronic medical records. The primary outcomes are the incremental cost-effectiveness ratios (ICER) based on the difference in mean costs and effectiveness between interventions and incremental cost-utility ratios (ICURs) based on health-related quality of life at post-treatment and 12-month follow-up. Secondary outcome measures include clinical symptoms, quality of life, functioning and treatment satisfaction. Bootstrap sampling will be used to assess the uncertainty of the results. Secondary moderation and mediation analyses will also be conducted. In addition, in sessions' number 1, 4 and 7 of both treatment arms, two questionnaires will be administered that collect therapeutic alliance and group satisfaction. The main study hypothesis is that adding TD-CBT to TAU in primary care will be more cost-effective than TAU plus PMR. In addition, these gains will be maintained in the 12-month follow-up. If it is successful, the dissemination of cost-effective treatment can help to overcome problems in accessing psychological treatment for emotional disorders in the context of an increasing demand for mental healthcare in primary care.

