Sessions 3-4: These sessions will be devoted to practice in cognitive restructuring and emotional self-regulation training. [66, 67] First, they will be instructed, in a general way, on what emotions are, how they manifest (i.e., at a cognitive-subjective, physiological and behavioural level) anxiety, fear or sadness; as well as in which situations these responses occur, which reactions help to improve adaptation to the environment or which do not, and which strategies are appropriate and which are not to regulate these reactions. It will also be explained how some emotional disorders can easily develop (e.g., when stress increases, uncontrolled anxiety reactions are triggered, too much importance is given to a physiological response that has no voluntary control and attention is focused on the physical sensations it produces). By means of case presentations, it will be shown how it is possible to detect and change distorted thoughts, irrational beliefs, threatening appraisals [68], cognitive biases [52], emotion regulation strategies, etc., which are associated with intense negative emotional states of anxiety, anger or other negative emotions in everyday life. Afterwards, we will work with concrete samples of emotional events experienced by patients in the last week and show them how they should approach these events from a new cognitive-emotional perspective that will help them better understand their errors and biases in emotion regulation, and how they can restore emotional self-regulation through changes in information processing (e.g., encouraging neutral information processing), encouraging neutral or positive information processing, using distraction, reducing the importance and magnification of the threat or loss, reducing ruminative processes, worry and biases of attention focused on the threat or loss, increasing positive self-instructions and perceived self-efficacy, etc.).

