**Treatment using relaxation techniques**

The treatment using Bernstein and Borkovec's progressive muscle relaxation technique will be applied by psychologists. Patients assigned to the control group, as in the experimental group, will receive 7 sessions of 1.5 hours duration in groups of approximately 10 people, spread over 24 weeks, with a greater temporal frequency at the beginning of the treatment (one session per week) and a progressive extension of the time interval between sessions as the treatment progresses.

Both groups, experimental and control, together with the treatments described above, will follow the usual treatment by their GP, according to their usual procedure, typically pharmacological treatment and unstructured support. The number of consultations received during the period of participation in the study will be taken into account.

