**APPLICABILITY AND USEFULNESS OF THE RESULTS AND ABILITY TO BE PROTECTED AND TRANSFERRED TO THE MARKET**

The planned clinical trial will provide clear evidence that, compared to treatment through relaxation, the incorporation of a group treatment for mental disorders commonly treated in Health Centres helps to reduce anxious, depressive and somatic symptomatology, as well as a reduction in the costs (direct and indirect) associated with anxiety, mood and somatoform disorders (Main hypothesis). PsicAP-Costs2 allows an immediate transfer of the results to the clinical context by providing the first experience in our context of a manualised transdiagnostic group treatment of short duration (7 sessions), which makes it easily applicable and generalizable to health centres in Cantabria and the rest of the NHS. The expected economic benefit in the reduction of psychopharmacological treatment costs and through the reduction of expenditure on sick leave and loss of productivity, which is a priority objective of the SCS in the management of TI associated with common mental disorders (Mental Health Plan of Cantabria 2015-2019), should make the dissemination among health professionals of this type of protocolised treatment, low cost and short duration, easily integrated into the routine care offered in Health Centres, profitable.

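### The cost numerator of the primary ICER and ICUR is given two scopes, and no section says which governs or who decides that use is disorder-related

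*Protocol*

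**What the plan says.** The Abstract sets the perspective and the data source: "The study will take a societal perspective", and "Data on health service use, including medication and days of absence from work, will be collected from electronic medical records". Neither sentence restricts use by cause.

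Outcome Measures, which defines the two primary outcomes, uses a different source and a narrower scope: "an ad hoc questionnaire will be used to collect emotional disorder-related healthcare data". The items listed are "public and private healthcare consultations, accidents, medical tests, and sick leaves in the past 3 months; psychotropic drugs or other medication". The second primary outcome takes the same numerator: "Cost-utility will be measured through the healthcare data collected above".

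The section on applicability and usefulness words the cost part of the main hypothesis as "a reduction in the costs (direct and indirect) associated with anxiety, mood and somatoform disorders (Main hypothesis", which is closer to the Outcome Measures scope.

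The relaxation-treatment section adds, for both arms, "The number of consultations received during the period of participation in the study will be taken into account", without saying whether or how this enters the cost calculation.

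**The concern.** The numerator decides what the primary endpoint is. Two analysts following the Abstract and Outcome Measures respectively would cost different events, and could reach different ICERs and ICURs from the same patients. Use that the questionnaire never asks about cannot be restored at analysis. This matters most for private care, which the electronic records may not hold.

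The narrow scope also needs someone to decide that an event belongs to the emotional disorder. That is hard in people who may enter the trial on somatic symptoms (PHQ-15, under Inclusion/Exclusion criteria). The protocol does not say who decides. If the participant does, the decision is made by someone who knows the therapy received: the assessors are blind, and patients are only asked not to reveal their group. Sessions 3-4 of TD-CBT teach how emotions show themselves in the body. One example given of how a disorder develops is that "too much importance is given to a physiological response that has no voluntary control". The short description of the relaxation arm mentions no such teaching. Attribution could therefore differ by arm while actual use does not, and the difference would pass into both primary ratios.

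**Working it through.** **The sections side by side**

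| Protocol section | What counts | Source | Who labels it |
|---|---|---|---|
| Abstract | Service use, medication, work absence; no restriction by cause | Electronic records | No label needed |
| Outcome Measures | Consultations, accidents, tests, sick leave, drugs; limited to the emotional disorder | Ad hoc questionnaire, 3-month look-back | Not stated |
| Applicability and usefulness | Direct and indirect costs tied to the disorders | Not stated | Not stated |

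Work absence appears in the first two rows, so there only the restriction and the source differ. The restriction is unclear even where it is made, since the list includes accidents and non-psychotropic medication. No section ranks the two sources or says how they combine.

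**Size of a possible label effect (illustration)**

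From the protocol: 150 per arm, and 2 x 150 = 300 agrees with the stated total. Everything else is assumed, because the protocol gives no cost mean, cost spread or attribution rate:

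- True mean cost C is the same in both arms.
- A share f of cost is labelled disorder-related under relaxation, and f + s under TD-CBT.
- CV is the standard deviation of labelled cost divided by its mean.

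Formulas:

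- Labelled means are fC and (f + s)C, so the false difference is sC, or s/f of the relaxation mean.
- With unrestricted counting the difference is C - C = 0.
- The standard error (SE) of the difference, relative to that mean, is CV x sqrt(2/150) = CV x 0.1155.
- With d = (s/f)/(CV x 0.1155), the actual error rate of a nominal two-sided 5% test of the cost difference is 1 - [Φ(1.96 - d) - Φ(-1.96 - d)].

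| f | s | s/f | d at CV 1 / 1.5 / 2 | Error rate at CV 1 / 1.5 / 2 |
|---|---|---|---|---|
| 0.3 | 0.05 | 16.7% | 1.44 / 0.96 / 0.72 | 30.3% / 16.1% / 11.1% |
| 0.3 | 0.10 | 33.3% | 2.89 / 1.92 / 1.44 | 82.3% / 48.6% / 30.3% |
| 0.5 | 0.05 | 10.0% | 0.87 / 0.58 / 0.43 | 13.9% / 8.9% / 7.2% |
| 0.5 | 0.10 | 20.0% | 1.73 / 1.15 / 0.87 | 41.0% / 21.1% / 13.9% |
| 0.8 | 0.05 | 6.25% | 0.54 / 0.36 / 0.27 | 8.4% / 6.5% / 5.8% |
| 0.8 | 0.10 | 12.5% | 1.08 / 0.72 / 0.54 | 19.1% / 11.1% / 8.4% |

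A negative s gives the same sizes with the opposite sign.

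In money, again only as illustration: an assumed EUR 1,500 per patient and a shift of 5 to 15 points give 1,500 x 0.05 to 1,500 x 0.15, or EUR 75 to 225. With an assumed standard deviation of EUR 2,000 for the counted cost, the SE is 2,000 x 0.1155 = EUR 231, so this is 0.3 to 1.0 SE.

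**The case against.** The other side has several good points.

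- **The Abstract lacks a qualifier but does not say that all use counts.** The two sources might be complementary. This is fair, but the protocol never says so, and the reader cannot tell which scope defines the endpoint.
- **A reader might infer that a societal perspective demands all-cause costs.** It does not. A perspective settles whose costs count, not which causes. Disorder-related costing that includes sick leave and private care is compatible with it, and the main hypothesis leans that way. An all-cause base case is therefore a choice and cannot be derived from the text.
- **A reader might take the consultation count in the relaxation section as a second all-cause cost definition.** It follows the description of usual GP care and defines no numerator.
- **A reader might use the 33-169% higher expenditure quoted under the cost of common mental disorders to size what the narrow scope leaves out.** That figure is total medical spending in people with chronic physical illness and comorbid anxious-depressive disorders, a group that the trial does not select.
- **A reader might infer that TD-CBT is known to push labelled costs upward.** Nothing shows this. The sessions do not teach patients to classify visits or sick leave. They also aim to reduce the weight given to threat, so the label could move either way. The relaxation content is too briefly described to prove a contrast between arms.
- **Classification rules often sit in an analysis plan.** That covers coding detail. It does not cover a scope that the protocol already fixes in two ways, or the wording of a questionnaire that is set before data are collected.

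The scope conflict and the unnamed classifier survive all of these. The bias by arm survives only as a possibility.

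**Conclusion.** The numerator of both primary ratios has two unreconciled scopes and two sources, and the rule for calling use disorder-related has no owner. That much rests on the text alone.

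Bias by arm is conditional. It needs the participant to apply the label, which a questionnaire with a 3-month look-back suggests but the protocol does not state. It also needs attribution to differ between arms. With f from 0.3 to 0.8, s from 0.05 to 0.10 and CV from 1 to 2, the false cost difference would be 6% to 33% of the relaxation mean. That is 0.27 to 2.9 SEs, with an error rate of 5.8% to 82%. A middle case (f = 0.5, s = 0.10, CV = 1.5) gives 20%, 1.15 SEs and about 21%. These ranges reflect the assumptions and are not estimates for this trial, and the protocol fixes neither sign nor size. Unrestricted counting removes this particular effect whatever the values. The point merits correction because the remedy is cheap and protects both primary outcomes.

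**What to change.** In Outcome Measures:

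1. Delete the qualifier that limits the questionnaire to use related to the emotional disorder, so that all use is collected.
2. State one governing scope, and align the Abstract and the main hypothesis with it.
3. Report both numerators: all-cause (electronic records plus private care from the questionnaire) and disorder-related. Name one as base case and the other as sensitivity analysis before any data by arm are seen. Either choice can be defended if it is stated.
4. Have existing staff blind to arm classify disorder-related use from record codes, not the participant. Private contacts without a record code need a written rule applied by the same staff.

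The cost is a change of protocol wording, one questionnaire item and some extra coding. All-cause costs vary more, so the interval for that numerator will be wider. Record codes do not fully isolate the disorder-related numerator from what patients say, because GPs enter the codes after hearing the patient and the protocol does not say that GPs are blind. The all-cause numerator does not depend on the label, which is a reason to report both.
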